## Abstract

**Objective:**

Magnifying endoscopy combined with narrow-band imaging endoscopy is an emerging method for early gastric cancer screening and diagnosis However, its effectiveness is closely related to the cleaning quality of the gastric mucosal preparation. *H. pylori* infection is a major risk factor for inadequate gastric mucosa cleaning quality preparation. Multiple medications are useful in helping patients with gastric mucosal cleansing preparations. This randomized controlled trial study protocol aims to investigate the effect of different combinations of medications on the quality of gastric mucosal cleansing in an *H. pylori*-infected population.

**Methods:**

This study is a prospective, randomized, single-blind, single-center trial. The subjects are patients who require magnifying endoscopy combined with narrow-band imaging and have evidence of *H. pylori* infection (a non-invasive diagnostic ^13^C urea breath test was used to examine the study subjects). These patients will be randomly assigned to the control group (Group A) and the experimental groups (Groups B, C, D, E, and F). Each group will consist of 44 patients, with a total of 264 patients expected to be enrolled. The core content of the drug preparation regimen for each group is as follows: Group A (control group) will take 10 ml of simethicone before the examination; Group B (experimental group) will take 20,000 units of pronase before the examination; Group C (experimental group) will take 600 mg of N-acetylcysteine before the examination; Group D (experimental group) will take 10 ml of simethicone +20,000 units of pronase before the examination; Group E (experimental group) will take 10 ml of simethicone + 600 mg of N-acetylcysteine before the examination; Group F (experimental group) will take 10 ml of simethicone + 20,000 units of pronase + 1 g of sodium bicarbonate before the examination. All group medications will be dissolved in 50 ml of warm water at 20–40°C. All patients will fast for ≥6 h and abstain from drinking for 2 h before the examination. The primary endpoint is the gastric mucosa cleanliness score. Secondary endpoints include the early detection rate of gastric cancer, polyp detection rate, adenoma detection rate, procedure time, number of irrigations, patient medication compliance, preoperative anxiety, incidence of adverse reactions, overall patient satisfaction, and willingness to undergo the examination again.

**Implications:**

The results of this research project are aimed at improving the quality of gastric mucosal cleansing preparations in the *H. pylori* population to meet the demand for early diagnosis and treatment prevention screening for early gastric cancer screening. The implementation of the results of the study and their inclusion in the guidelines may reduce economic expenditures by reflecting a reduced need for social and health care services.

**Clinical Trial registration:**

Chinese Clinical Trial Registry (ChiCTR). Number of identification: (ChiCTR2400087510).

## 1 Introduction

In the twenty-first century, cancer remains a major social, public health and economic problem worldwide. According to the latest report of the International Agency for Research on Cancer (IARC), gastric cancer accounts for 4.9% of cancer incidence and 6.8% of cancer deaths, ranking fifth globally in terms of incidence and mortality (1). As we all know, *H. pylori* infection is closely related to digestive diseases such as chronic gastritis, peptic ulcer, gastric cancer and mucosa-associated lymphoid tissue lymphoma. The World Health Organization has classified *H. pylori* as a group I carcinogen for human gastric cancer. Studies have shown that the global *H. pylori* infection rate is 48.5%, and the *H. pylori* infection rate in China is as high as 50% (2). *H. pylori* is considered to be the most important part of the risk factors associated with GC, and it has been estimated that more than 78% of the population with GC is directly related to *H. pylori* infection (3). Therefore, selection of patients with suspected *H. pylori* infection because they are at a higher risk of gastric cancer compared to the general population, and it is also important for accurate gastric cancer risk stratification.

The survival period of gastric cancer patients is closely related to the time of clinical diagnosis (early stage can be cured, while late stage can only be treated with palliative symptomatic therapy, etc.). According to the developmental pattern of gastric cancer, the whole course of the disease usually ranges from 5 to 15 years, which provides a valuable window of time for early clinical screening and subsequent treatment. However, the key problem is that early gastric cancer symptoms are not obvious or even asymptomatic. Most of the patients are already in the middle or late stage of gastric cancer when they visit the doctor, and early diagnosis and treatment is the key to early gastric cancer. Some studies have shown that the 5-year survival rate of gastric cancer can reach more than 90% after high-quality upper gastrointestinal endoscopy screening and treatment (4–7).

Plain white light endoscopy is inadequate for the diagnosis of early precancerous lesions and EGC. Especially in the *H. pylori* population Narrowband imaged magnifying endoscope (ME-NBI) is a combination of magnifying endoscope and narrowband imaging, due to its unique optical method, fine mucosal structures and microvessels can be observed using an 80 × magnifying endoscope. It is specifically designed for the detection of early gastric cancer (8).

A clear visualization of the gastric mucosa is critical to prevent the oversight or misdiagnosis of early-stage gastric cancer lesions (9, 10). During gastrointestinal endoscopy, the quality of the examination can be significantly compromised by secretions on the mucosal surface, including saliva, bubbles, and mucus. Inadequate preparation of the gastric mucosa not only impairs visual clarity but also heightens the risk of overlooking small lesions and decreases the detection rate of upper gastrointestinal tumors. Conventional cleaning methods, such as repeated suction or saline irrigation during the procedure, not only extend the duration of the operation but also exacerbate patient discomfort and increase the risk of intraoperative complications. Therefore, ensuring thorough preparation for gastric mucosa cleanliness is essential for enhancing both the efficiency of endoscopy and diagnostic accuracy.

To achieve optimal visualization of the gastric mucosa, it is essential to administer preoperative medications aimed at eliminating mucus and foam within the stomach (11). Due to variations in clinical practices across different medical institutions, there is currently no consensus among major endoscopy centers regarding the necessity and selection criteria for preoperative medication regimens for gastric mucosa preparation. However, studies have confirmed that combination therapy yields superior results (12, 13). Research into enhancing the quality of gastroscopy has a long history. American scholar J. Alfred Rider first proposed the use of antifoaming agents to improve the visibility of the gastric mucosa in the 1960s (14). Simethicone is a non-ionic surfactant that effectively reduces the surface tension of liquids, thereby facilitating the rupture and expulsion of gas bubbles within the stomach. This action significantly enhances the visual field during endoscopic procedures. Its application in gastroscopy was first documented in 1954 (15), and it has since become widely utilized in preoperative preparations to improve the detection rate of minor lesions (16). Pronase is a glycoprotein hydrolase that effectively degrades the mucus layer on the surface of the gastric mucosa, thereby enhancing endoscopic visibility (17). Research has demonstrated that this agent can also diminish gastric wall echogenicity during endoscopic ultrasound examinations, leading to improved image quality (18). However, due to the high acidity present in the stomach, Pronase's activity may be constrained; thus, its use in conjunction with sodium bicarbonate or scopolamine butylbromide is recommended to optimize its functional environment. Furthermore, existing clinical studies indicate that Pronase can enhance visual clarity within the gastric fundus and body, significantly increasing the detection rate of small lesions such as erosions and ulcers (19). N-acetylcysteine has the ability to disrupt disulfide bonds in mucus, thereby reducing its viscosity and improving mucosal visualization during gastroscopy (20). Research indicates that the combination of this medication with simethicone significantly enhances the imaging quality of gastroscopy while decreasing the need for irrigation fluid (16, 21). Moreover, when compared to traditional mucolytic agents such as chymotrypsin and pronase, N-acetylcysteine may demonstrate superior efficacy; however, further studies are required to establish its safety across diverse populations.

Current research predominantly concentrates on pre-endoscopic medication regimens for the general population. In contrast, studies addressing optimal medication protocols for high-risk groups susceptible to gastric cancer, such as patients with *H. pylori* infection, remain relatively limited. This limitation affects the accuracy of our screening for high-risk groups of early gastric cancer, hence, there is a need to conduct a study to address this clinical issue.

## 2 Objective

This study employs a single-center randomized controlled trial design, aiming to investigate whether the combined use of multiple defoaming agents and mucolytic agents, including simethicone, pronase, N-acetylcysteine, and sodium bicarbonate, prior to magnifying endoscopy with narrow-band imaging, can significantly enhance the clarity of the gastric mucosa in patients infected with *H. pylori*. Additionally, we have incorporated several observational metrics into the protocol to assess the safety of the procedure and the effectiveness of reducing the operation time.

## 3 Materials and methods

### 3.1 Study design

The study is a prospective, single-center, single-blind, randomized controlled study. It is planned to be conducted from September to December 2024 at the Center for Gastrointestinal Endoscopy, Affiliated Hospital of Zunyi Medical University, Zunyi, Guizhou Province, China. The endoscopists participating in this study are experienced endoscopists who perform more than 800 magnified gastroscopy narrow-band imaging techniques per year. The study protocol was approved by the Biomedical Research Ethics Committee of the Affiliated Hospital of Zunyi Medical University and registered. The patient enrollment flowchart is shown in Figure 1.

**Figure 1 F1:**
[figure not shown]
Flowchart of the patient enrolment procedure.

### 3.2 Blinding

Due to the nature of the intervention, all participants and endoscopists involved in the study were blinded to ensure the authenticity and objectivity of the data. The endoscopic procedures were performed by a single endoscopist with over 1000 ME-NBI procedures per year, and the quality of acquired images was analyzed and evaluated by two gastroscopy experts with ≥10 years of experience (with more than 500 cases reviewed). Initial baseline data collection will commence, with two other well-trained researchers (blinded to the groups) responsible for data collection. The investigator responsible for implementing the intervention will not be involved in the data collection process.

### 3.3 Participants and recruitment

#### 3.3.1 Eligibility criteria

##### 3.3.1.1 Inclusion criteria

Age ≥18 years and ≤65 years male or female (22);According to the diagnostic criteria for *H. pylori* infection (23), a non-invasive diagnostic ^13^C urea breath test was used to examine the study subjects. Patients were instructed to avoid using antibiotics, bismuth preparations, or proton pump inhibitors for 2 weeks prior to the test. The labeled urea solution was administered: typically, a ^13^C-labeled urea solution at a dose of 75 mg/m^2^ of body surface area. Breath samples were collected: baseline breath samples were taken to measure the baseline values. After consuming the labeled urea, breath samples were collected at fixed intervals (10 min). The abundance of ^13^C in the breath samples was measured using mass spectrometry. The results were expressed as δ values (i.e., the ratio of ^13^C/^12^C), with a threshold of 3.5‰; a δ value above this threshold was considered positive. A positive result: δ value > 3.5‰, indicating *H. pylori* infection. A negative result: δ value ≤ 3.5‰, indicating no *H. pylori* infection.No previous magnified gastroscopy with narrow-band imaging;Ability to sign an informed consent form on their own.

##### 3.3.1.2 Exclusion criteria

A confirmed diagnosis or high suspicion of gastric cancer or other malignant tumors of the gastrointestinal tract;Have a history of gastric surgery or other surgeries affecting gastric function;Having serious heart, liver, kidney, and other organ insufficiency or other serious systemic diseases;Having factors affecting the clarity of the gastric mucosa, such as heavy smoking, alcohol consumption, and taking non-steroidal anti-inflammatory drugs (24– 26);Having received *H. pylori* eradication therapy or other antimicrobial therapy within the past month;Pregnant or lactating women.Allergy to any of the study medications.

#### 3.3.2 Sample size

The gastric mucosa clarity score was used as the primary observation indicator, and the sample size calculation formula for multiple group means was evaluated using PASS software. The significance level (α) was set at 0.05 and β at 0.1. The estimated minimum sample size required for each group was 40 cases, totaling 240 cases, with an expected dropout rate of 10%. Both the control and experimental groups had 44 cases each. The calculation formula is as follows:

$$n=\frac{\varphi^{2}\left(\sum_{j=1}^{k}s_{j}^{2}/k\right)}{\sum_{j=1}^{k}{\left(X_{j}-X\right)}^{2}/\left(k-1\right)}.$$

#### 3.3.3 Recruitment

The recruitment exercise was carried out between September and December 2024, and a total of 264 participants were recruited to administer outpatient screening at the Digestive Endoscopy Center. To effectively screen eligible participants, study team members will work with outpatient staff to review medical records for patients with high blood pressure, diabetes, or dyslipidemia. Patients who meet the eligibility criteria will be contacted by one of the researchers to gauge their interest in learning more about the research project. Participants will then be contacted by another skilled researcher at the Endoscopy Center via investigator phone over 2 days to provide detailed information about the study. Qualified subjects will be recruited after a signed informed consent form is obtained.

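### Section 3.3.3 searches records for high blood pressure, diabetes or dyslipidemia, which are not eligibility criteria; used as a filter, this would narrow the sample to a subgroup of H. pylori-positive patients

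*Protocol article*

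**What the plan says.** The Abstract (Methods) defines the trial population: "The subjects are patients who require magnifying endoscopy combined with narrow-band imaging", with evidence of H. pylori infection.

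Section 3.3.1.1 turns this into entry criteria: "Age ≥18 years and ≤65 years male or female"; a 13C urea breath test with a 3.5‰ threshold, where "a δ value above this threshold was considered positive"; "No previous magnified gastroscopy with narrow-band imaging"; and the ability to give one's own consent. Section 3.3.1.2 lists the exclusions. The one nearest to the present topic is "Having serious heart, liver, kidney, and other organ insufficiency or other serious systemic diseases".

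Section 3.3.3 then describes how candidates are found: "study team members will work with outpatient staff to review medical records for patients with high blood pressure, diabetes, or dyslipidemia". The next step is that "Patients who meet the eligibility criteria will be contacted by one of the researchers to gauge their interest". When it describes the search, the section mentions neither H. pylori, nor the breath test, nor an ME-NBI indication.

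**The concern.** A recruitment section should lead staff to the people whom the eligibility section describes. This one names three chronic conditions that have no role in the trial: they are absent from the rationale, the objective, the criteria, the outcomes and the discussion. A team that followed the sentence as a filter would never look at the records of H. pylori-positive ME-NBI patients who have none of the three.

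What is at stake is the population to which the result applies. The Abstract hopes for uptake in guidelines for the H. pylori population, and the Discussion speaks of groups at risk of gastric cancer. If the sample were in fact a cardiometabolic subset of that population, those statements would go beyond the data, and the limitations in the Discussion would not tell the reader so.

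**Working it through.** The protocol states no figure on this point, so the check is a comparison of sections.

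| Section | Who is described | Any of the three conditions? |
|---|---|---|
| Abstract, Methods | Patients needing ME-NBI, with H. pylori infection | No |
| 2 Objective | H. pylori-infected patients before ME-NBI | No |
| 3.3.1.1 Inclusion | Age 18–65, breath test above 3.5‰, no earlier ME-NBI, own consent | No |
| 3.3.1.2 Exclusion | Includes serious organ insufficiency or serious systemic disease | Not named |
| 3.3.3 Recruitment | Outpatient records with high blood pressure, diabetes or dyslipidemia | **Yes, all three** |
| 3.6.1 Primary outcomes | H. pylori-infected individuals | No |
| 4 Discussion | Gastric cancer risk groups, H. pylori-positive patients | No |

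**Step 1: can the sentence be read in line with 3.3.1?** If the review selects such patients in, it uses conditions that are not inclusion criteria. If it screens them out, it removes patients whom 3.3.1.2 does not exclude, since none of the three is named there. Both readings conflict with 3.3.1.

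**Step 2: who would be enrolled?** The record review comes first and eligibility second. Under a strict filter the sample is therefore the intersection: patients who meet 3.3.1 *and* have at least one of the three conditions. All are still H. pylori-positive.

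**Step 3: what happens to the estimates?** Let π be the share of the target population with at least one of the conditions, s the share in the sample, d₁ the between-arm difference in cleanliness score in patients with a condition, and d₀ the difference in those without.

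- Target: π·d₁ + (1 − π)·d₀
- What the trial estimates: s·d₁ + (1 − s)·d₀
- Gap: (s − π)·(d₁ − d₀)

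Under a strict filter s = 1, and the gap is (1 − π)·(d₁ − d₀). It vanishes if the effect is the same with and without the conditions (d₁ = d₀), if everyone in the target population has one (π = 1), or if the filter was not applied and the sample has s = π. The protocol gives none of π, s, d₁ or d₀, so no number can be attached.

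**Step 4: is the comparison between arms biased?** No. The filter acts before randomisation, so the expected s is the same in all six groups. Each contrast is a valid estimate for the population actually enrolled. Only the transfer to the wider population is affected.

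**The case against.** The strongest reply is that the sentence is a stray one and does not govern how patients are found. Three things support this.

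- Section 3.3.3 does not call the record review the only route, and the sentence before it places recruitment in outpatient screening at the endoscopy centre.
- Section 3.4 orders the randomisation envelopes by examination appointment, and section 3.5 numbers patients from the day's screening list. Both suggest that the endoscopy schedule is the working source.
- Sections 3.3.3 and 3.4 still require that the eligibility criteria be met before contact and before randomisation.

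This stands as far as it goes. It makes it uncertain that the filter shaped the sample, and it rules out several stronger readings that a reader might infer:

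- *That the trial enrols people other than the H. pylori population.* It does not; the breath test remains an entry condition.
- *That the filter clashes with the exclusion of serious systemic disease.* That exclusion is limited to serious disease, and the protocol does not say that any of the three conditions is serious in itself. A patient can have one and be eligible.
- *That mainly younger adults would be missed, or that accrual of 264 patients in four months is endangered.* Either claim needs prevalence or clinic-volume figures, and the documents give none.

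The reply does not remove the contradiction. The sentence is a specific instruction in the section that governs recruitment, and nothing elsewhere withdraws or explains it. Nor is it a detail lost through condensation in a journal article: the text affirmatively states a search rule that does not match the criteria. If practice differed, the protocol misreports how participants were found.

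**Conclusion.** Section 3.3.3 is wrong as written and must be reconciled with 3.3.1. The conclusion rests on the text alone: the three conditions are named in the search step and nowhere else.

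The consequence is conditional. *If* the record review was used as a filter, the sample is a subgroup of H. pylori-positive ME-NBI patients, and the results do not represent the whole population named in the Abstract, section 2, section 3.6.1 and the Discussion. How far the estimates would shift depends on how common the conditions are and on whether the effect differs by them, both unknown here. If the filter was not used, the fault is one of description only. In either case the randomised comparison is unbiased, and this point does not affect the error rate or the blinding.

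**What to change.** Amend the one sentence in 3.3.3 so that candidates are identified by the trial's own entry conditions: outpatients scheduled for ME-NBI with a positive 13C urea breath test, then checked against 3.3.1. No particular sampling scheme beyond this is needed to resolve the contradiction.

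Section 3.3.3 mixes past and future tense about recruitment, so the text does not settle whether enrolment had taken place. The sponsor should therefore state which method was used. If the filter was applied, the report should give the number of participants who came through it and limit the population claim to match. Medical history is already among the baseline data in section 3.6; if it covers the three conditions, tabulating them by group would show readers whom the sample represents.

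The cost is one sentence in the protocol and, if the filter was used, one count and a narrower statement of the population in the report. The breath test is already required for entry, so no procedure is added, and neither the sample size nor the analysis changes.

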### 3.4 Randomization and allocation concealment

In this study, a table of 264 random numbers of cases was randomly generated by one endoscopy staff member using the computer SPSS and stored in a sealed envelope by another endoscopy staff member in the order in which the patients were scheduled for examination. When a patient who meets the inclusion criteria agrees to participate in this study, we will open the envelopes in order and randomize the patients into 6 subgroups A.B.C.D.E.F according to the numbers shown in the envelopes, with a randomization ratio of 1:1:1:1:1:1. Two staff members were not involved in this study. None of the endoscopic operators who performed the examination know which subgroup medication the patient was taking, the purpose of which was to ensure the truthfulness and objectivity of the data. Endoscopy operations were performed by the same endoscopist with more than 1,000 ME-NBI operations/year, and the quality of the acquired images was analyzed and evaluated by two gastroscopy reading specialists with ≥10 years of experience (>500 readings).

